### Randomisation and blinding

Allocation of patients in a 1:1 ratio to either the active or placebo group will be based on computer generated random numbers using a central randomisation website hosted by the University of Tasmania. Block randomisation, using a block size of 10 (5 in each arm) will be used. This means that of every 10 patients randomised, 5 will receive active and 5 placebo. The randomisation will be stratified by study site. This will be conducted by a staff member at each study site with no direct involvement in the study.

The randomised controlled trial will be a double-blind one, with both patients and investigators assessing outcomes blinded to treatment allocation. Allocation concealment and double blinding will be ensured by 1) the use of identical IV infusions for each group; 2) objective measures of knee structural changes being made by trained observers blinded to group allocation; and 3) subjective measures being taken by research nurses blinded to group allocation.

Emergency unblinding will be allowed in limited situations that impact on the safety of study patients. Code-break for the full randomisation schedule will be maintained by the University of Tasmania. Patients who are unblinded will be withdrawn from treatment but will continue to be followed as per the planned follow-up schedule.

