### Sample size calculations

#### Primary outcome

In our pilot study [40] we found that zoledronic acid significantly reduced the size of BMLs over 6 months compared to placebo. Therefore our sample size calculations for this trial were modelled based on the assumption that a decrease in BML size will translate to a reduction in cartilage volume loss over time. This assumption is valid based on the unequivocal evidence from observation data demonstrating that BMLs predict cartilage volume loss over time [14–17, 38, 54, 57–59].

The changes in BML area seen in our pilot study were − 198.6 mm^2^ (zoledronic acid treatment) and − 22.8 mm^2^ (placebo) with regression root mean square error of 261.5 mm^2^ (i.e. standard deviation (SD)) [40], at 6 months. Unpublished observational data from our Tasmanian Older Adult Cohort (TASOAC) study allowed us to model the effect a decrease in BML size would have on tibiofemoral cartilage volume loss over 24 months. Using follow-up data for 120 TASOAC participants with BMLs, we used linear regression to estimate the relationship between absolute change in tibiofemoral cartilage volume and final BML area with adjustment for age, sex, BMI and length of follow-up. The results can be used to predict each subject’s two-year change in tibiofemoral cartilage volume from their final BML area, and the change when final BML area is reduced by 198.6 mm^2^ (expected under treatment) or 22.8 mm^2^ (expected under placebo). To take account of individual variation, the calculations were repeated in 1000 replications with the exact changes in final BML area replaced by random values of 198.6 mm^2^ (treatment) firstly and 22.8 mm^2^ (placebo) secondly, and with SD 261.5 mm^2^ in each case. The resulting estimates of tibiofemoral cartilage loss, which are expected from the 6 month changes in BML area, were − 824.0 mm^3^ (SD 273.0) in the treatment group and − 928.3 mm^3^ (SD 272.3) in the placebo group. With this difference, 132 patients (allowing for 20% drop out over 24 months) recruited to each arm of the trial will provide 80% power with 5% probability of type I error (alpha = 0.05). This estimate is conservatively based on 6-month change in BML area for *n* = 59 patients in our pilot study [40] and assumes no further improvement in BMLs after this time (although they may continue to reduce with zoledronic acid over 24 months).

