#### Secondary outcome

For our secondary outcomes (improvement in pain and reduction in BML size) a sample size of 132 patients in each arm will provide 98.9 and 99.6% power to detect the adjusted treatment differences in knee pain scores and BML area respectively that were observed in our pilot study [40].

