### Statistical analysis

The primary analyses will be intention-to-treat analyses of primary and secondary outcomes. Per protocol analyses will be performed as the secondary analyses.

Changes in absolute tibiofemoral cartilage volume, knee pain and BML size will be analysed using a linear mixed model with treatment, month and their interaction (treatment × month) as covariates. The correlation within trial centres and the repeated measures will be addressed using trial centre and patient identification as random intercepts. Month will be treated as random effect to allow different treatment effects among patients over time. Change in outcome measures within each group and difference of the changes between groups from baseline to follow-up will be calculated using linear combinations of the estimated coefficients. If there are baseline imbalances between treatment groups, we will consider adjusting for them based on whether we regard the imbalance as clinically significant. Missing data caused by loss to follow-up and nonresponses will be addressed by adding baseline complete variables that can explain the missingness to the regression models.

Secondary analysis for missing data will be performed using multiple imputation by chained equations. Baseline variables with complete data will be used for data imputation assuming missing at random.

Pre-specified stratified analyses will be performed to examine which subgroups may respond better to treatment. Potential stratification variables include radiographic knee OA and co-pathology present on MRI. Statistical significance will be set as a two-sided *P* value < 0.05.

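### The mixed model does not condition on the baseline outcome value, and its covariates are left to judgement on observed imbalance or missingness, so the primary model is not fixed in advance

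*Protocol article*

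**What the plan says.** Under Statistical analysis, the protocol article analyses cartilage volume, knee pain and BML size with one linear mixed model. Its fixed effects are treatment, month and treatment by month. Centre and patient are random intercepts, and month is also a random effect. The treatment effect is the between-arm difference in change from baseline, formed from the model coefficients. No baseline value appears as a covariate.

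Further covariates enter in two ways:

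- Imbalance: "If there are baseline imbalances between treatment groups, we will consider adjusting for them based on whether we regard the imbalance as clinically significant".
- Missingness: absent values are to be handled by "adding baseline complete variables that can explain the missingness to the regression models".

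Neither route names variables or sets a threshold. Multiple imputation from complete baseline variables is planned as a secondary analysis. The test is fixed: "Statistical significance will be set as a two-sided *P* value < 0.05".

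**The concern.** Because the treatment main effect is kept, the two arms have separately estimated baseline means. Baseline is subtracted through the change contrast, but it is not used as a predictor of follow-up. That usually gives up precision which the trial has already paid for.

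The covariate rules raise a separate problem. Whether an imbalance counts is a judgement on the observed data, and even a judged imbalance leads only to considering adjustment. Variables that explain missingness can be recognised only once data are missing. As stated, several primary models remain possible.

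The form of adjustment is also open. With complete data at two times, a baseline covariate added only as a main effect shifts both of a patient's values equally and cancels from the change. It would leave the treatment-by-month estimate where it was. To matter, the covariate must be allowed to act on follow-up or by month.

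**Working it through.** **1. The plan's own figure.** Inputs from Sample size calculations, Primary outcome: changes of minus "824.0 mm^3^ (SD 273.0) in the treatment group" and minus "928.3 mm^3^ (SD 272.3) in the placebo group", and "132 patients (allowing for 20% drop out over 24 months) recruited to each arm of the trial will provide 80% power". Alpha is 0.05 two-sided and allocation is 1:1.

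- Difference = 928.3 − 824.0 = 104.3. Pooled SD = √((273.0² + 272.3²)/2) = 272.65.
- n per arm = 2 × (272.65 × (1.960 + 0.842)/104.3)² = 107.3, so 108 evaluable. 108/0.8 = 135 recruited, against 132 stated.
- 132 × 0.8 = 105.6 evaluable. Power at 105-106 per arm is 79.2-79.5%, against 80% stated.

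The stated size reproduces closely as a plain comparison of two mean changes. It does not rely on baseline adjustment.

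**2. What the model estimates.** Cartilage volume is calculated at screening and 24 months only. With complete data at two times and a free baseline difference between arms, the interaction equals the raw difference in mean change.

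**3. Precision.** Let σ² be the variance at each time and ρ the baseline to follow-up correlation (**assumed; not in the article**).

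- Change score: 2σ²(1 − ρ). Conditional on baseline: σ²(1 − ρ²). Ratio = (1 + ρ)/2.

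| ρ | 0.3 | 0.4 | 0.5 | 0.6 | 0.7 | 0.90 | 0.95 | 0.98 |
|---|---|---|---|---|---|---|---|---|
| Variance ratio | 0.65 | 0.70 | 0.75 | 0.80 | 0.85 | 0.95 | 0.975 | 0.99 |

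For cartilage volume, taking 272.65 as the SD of change and 106 evaluable per arm, power moves from 79.5% to 81.5%, 80.5% and 79.9% at ρ of 0.90, 0.95 and 0.98. For pain or BML size at ρ of 0.3-0.6, variance falls by 20-35%. Standard errors fall by 11-19%, since √0.80 = 0.89 and √0.65 = 0.81.

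**4. Unequal variances.** Entry requires pain of at least 40 mm, which may narrow the baseline spread. With k = baseline SD / follow-up SD, the ratio is (1 − ρ²)/(k² + 1 − 2ρk).

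- k = 0.7 (assumed), ρ = 0.3: 0.91/1.07 = 0.85. ρ = 0.5: 0.75/0.79 = 0.95. ρ = 0.6: 0.64/0.65 = 0.985.
- k = 0.85 (assumed), ρ = 0.3: 0.91/1.2125 = 0.75. ρ = 0.6: 0.64/0.7025 = 0.91.

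The gain for pain could then be 9-25% (k = 0.85) or only 1.5-15% (k = 0.7).

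**5. How often an imbalance would appear.** The standard error of a standardised baseline difference is √(2/132) = 0.123. A chance difference above 0.2 SD has probability 10% per variable. For at least one of 5 independent variables it is 42%, and for one of 10 it is 67%. The 0.2 SD threshold is illustrative.

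**6. Type I error.** Simulation under no effect: two time points, 106 per arm, 40,000 replicates per setting, imbalance in the baseline outcome value with thresholds of 0.1 and 0.2 SD. Figures are rates over all simulated trials. Monte Carlo standard error is about √(0.05 × 0.95/40,000) = 0.1 point.

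| ρ | Adjust mechanically if imbalanced | Keep smaller p if imbalanced | Always keep smaller p |
|---|---|---|---|
| 0.5 | 3.9% | 5.4-6.2% | 7.3-7.5% |
| 0.7 | 4.2-4.3% | 5.3-5.9% | 6.7-6.8% |
| 0.95 | 4.8-4.9% | 5.1-5.4% | 5.7% |

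Either fixed model, always change score or always adjusted, gave 4.9-5.2%.

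**The case against.** The strongest reply is that little is lost on the primary outcome. If cartilage volume tracks strongly over time, conditioning on baseline saves at most about 5% of variance. That stands. A reader might infer that the primary analysis wastes substantial precision, but the article gives no correlation that would support this.

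A reader might also infer that the imbalance rule itself inflates type I error. It does not: applied mechanically it is slightly conservative. The criterion is clinical judgement, not a significance test. The article does not say that the judgement is made after outcomes are known, and baseline balance can be assessed without them. An analysis plan could still fix the timing and the variables. What remains is that the rule as stated is discretionary, and that the missingness route depends on follow-up data.

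A third inference is that the planning figures contradict the model, because Sample size calculations, Secondary outcome, cites "power to detect the adjusted treatment differences in knee pain scores and BML area". What those differences were adjusted for is not stated in the article, so a contradiction cannot be shown. For the primary outcome, age, sex, BMI and length of follow-up adjust an observational cohort regression, not a treatment comparison.

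Finally, (1 + ρ)/2 is a two-time-point, equal-variance result, while pain is measured at six times under a random-effects model. The 20-35% is therefore indicative. On the plan's own figures the secondary outcomes have 98.9% and 99.6% power, so extra precision there mainly narrows intervals.

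**Conclusion.** The point holds in a limited form. The model gives baseline a free arm difference and does not condition on it, and both covariate routes leave the primary model open as the article states it. The imbalance rule brings no gain in validity. Its cost is discretion, worth roughly 0.1 to 1.2 percentage points of type I error if the better result were kept whenever an imbalance was seen.

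The precision forgone rests on assumed correlations and variances. It is probably small for cartilage volume. For pain and BML size it is moderate with equal variances, and smaller for pain if the entry criterion compresses baseline spread. The stated sample size is not called into question. This is an inexpensive improvement that should be made, not a flaw that invalidates the analysis.

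**What to change.** In every primary and secondary model, whatever the observed balance, specify one of the following:

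- Constrain the arms to a common baseline mean by dropping the treatment main effect at baseline, so that they differ only at follow-up.
- Model follow-up values only, with the baseline value of that outcome as a covariate allowed to act by month. Baseline must then leave the response, so that it is not on both sides.

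Keep site in the model as already planned. Replace the imbalance sentence with this rule, and report any imbalance-driven adjustment as a labelled sensitivity analysis. Keep missingness predictors in the primary model only if they are named before unblinding. Otherwise use them in the multiple imputation already planned. Age, sex and BMI are optional. Any such covariate should be named in advance and, if baseline stays among the responses, allowed to act by month.

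The cost is a small change in model specification. No new data are needed.

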### Study procedure and time points

Research nurses will first conduct screening over the telephone. If early checks of study eligibility are favourable, study patients will be booked in for a face-to-face screening visit to further determine eligibility and explain what is involved in the study. At the face-to-face visit, patients will complete questionnaires, have a knee x-ray and MRI, a blood test, and a clinical assessment by a study doctor to ensure inclusion criteria are met. The study knee will be defined as the one with symptomatic OA meeting all inclusion criteria.

Table 1 outlines the schedule of assessments. After screening, there will be 4 study visits (month 0, 6, 12 and 24). The same researcher nurses, who are blinded to treatment allocation, will measure all clinical variables, administer questionnaires, monitor compliance, and record adverse events at these visits. Additional questionnaire mail outs will occur at months 3 and 18. Infusions will occur at months 0 and 12; MRI scans will occur at screening, month 6 and 24; knee x-ray will be performed at screening; blood samples are taken at screening and 6 months, and urine samples are taken at baseline and 6 months. Three days following the infusion, patients are contacted by phone interview to assess side effects of acute phase reactions.

**Table 1 Tab1:** Schedule of assessments

	Screening	Baseline (Month 0)	Day 3 Post-Infusion	Month 3	Month 6	Month 12	Day 3 Post-Infusion	Month 18	Month 24
Informed consent	x								
Clinical examination	x								
Knee x-ray	x								
Bloods	x				x*				
Knee MRI	x				x				x
Randomisation		x							
Clinic measures									
Leg strength		x			x	x			x
Height and weight		x			x				x
First void fasting urine		x*			x*				
Infusion		x				x			
Questionnaire measures									
Demographics (sex, date of birth)	x								
Knee VAS	x	x		x	x	x		x	x
Knee WOMAC		x		x	x	x		x	x
Medication use	x			x	x	x		x	x
Knee surgery	x			x	x	x		x	x
Knee joint injection					x	x		x	x
Safety (adverse events)		x	x	x	x	x	x	x	x
Acute phase reactions			x				x		
Hand VAS		x		x	x	x		x	x
Back VAS		x		x	x	x		x	x
AQoL-4D		x			x				x
Overall change in pain and function									x
Treatment guessing									x

*Only being performed at the Hobart, Melbourne and Sydney study sites

*MRI* magnetic resonance imaging, *VAS* visual analogue scale, *WOMAC* Western Ontario and McMasters Universities Osteoarthritis Index, *AQoL-4D* The Assessment of Quality of Life

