Melbourne	3.0 T whole-body MR unit (Philips, Achieva, Medical Systems), using a commercial 16-channel transmit receive knee coil	T1-weighted fat-saturated 3D gradient-recalled acquisition; flip angle 15 degrees; repetition time 25.9 msec; echo time 9.2 msec; field of view 16 cm; 320 × 320 matrix; slice thickness 0.5 mm	Proton density fat-saturated 2D fast spin echo sequence; flip angle 90 degrees; repetition time 3814 msec; echo time 25 msec; field of view 16 cm; 720 × 720 matrix; slice thickness 2.5 mm
Sydney	1.5 T whole-body MR unit (Siemens, Aera) using a dedicated 15-channel transmit-receive knee coil	T1-weighted fat-saturated 3D gradient-recalled acquisition; flip angle 30 degrees, repetition time 31 msec; echo time 6.8 msec; field of view 16 cm; 512 × 512 matrix; slice thickness 1.5 mm	Proton density fat-saturated 2D fast spin echo sequence; flip angle 150 degrees; repetition time 3830 msec; echo time 39 msec; field of view 16 cm; 512 × 512 matrix; slice thickness 3 mm
Adelaide	1.5 T whole-body MR unit (Siemens, Aera) using a dedicated 15-channel transmit-receive knee coil	T1-weighted fat-saturated 3D gradient-recalled acquisition; flip angle 30 degrees, repetition time 14.7 msec; echo time 6.74 msec; field of view 16 cm; 448 × 448 matrix; 1 excitation; slice thickness 1.5 mm	Proton density fat-saturated 2D fast spin echo sequence; flip angle 180 degrees; repetition time 3200 msec; echo time 39 msec; field of view 16 cm; 320 × 320 matrix; 1 excitation; slice thickness 3 mm

Knee femoral cartilage volume will be determined on the sagittal T1-weighted sequences by means of image processing on an independent workstation using Cartiscope™ (ArthroLab Inc., Montreal, Quebec, Canada), as previously described [46–48]. The segmentation of the cartilage-synovial interfaces will be carried out with the semi-automatic method under reader supervision and with corrections when needed. Cartilage volume will be evaluated directly from a standardised view of 3D cartilage geometry as the sum of elementary volumes. In our previous study, we demonstrated a CV of approximately 2% [46]. The cartilage volume assessment will be done for the medial and lateral condyles delineated by the Blumensaat’s line [48].

Tibiofemoral cartilage volume will be calculated as the sum of both the tibial and femoral compartments at screening and 24 months.

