### Withdrawal

If patients withdraw from the study before 24 months of follow-up, the reason and date will be recorded. Patients who withdraw after a minimum of 9 months will be requested to have a third MRI scan on their study knee.

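### The stated multiple imputation uses baseline variables under missing at random, as the primary model already does, so for cartilage volume it would add little

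*Protocol article*

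**What the plan says.** All of the missing-data plan is in the protocol article, Methods, Statistical analysis, with related facts in three other sections.

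- **Primary model.** Cartilage volume, knee pain and BML size "will be analysed using a linear mixed model with treatment, month and their interaction (treatment × month) as covariates".
- **Missing data in the primary model.** Missing values are to be "addressed by adding baseline complete variables that can explain the missingness to the regression models".
- **Secondary analysis.** "Secondary analysis for missing data will be performed using multiple imputation by chained equations". On predictors and assumption: "Baseline variables with complete data will be used for data imputation assuming missing at random". No other predictor is named.
- **Primary outcome.** "Tibiofemoral cartilage volume will be calculated as the sum of both the tibial and femoral compartments at screening and 24 months".
- **Imaging schedule (Study procedure and time points).** "MRI scans will occur at screening, month 6 and 24". BML size is measured at all three scans.
- **Early leavers (Withdrawal).** "Patients who withdraw after a minimum of 9 months will be requested to have a third MRI scan on their study knee". No use of this scan in the analysis is described.
- **Dropout (Sample size calculations).** 20% over 24 months.

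**The concern.** A second missing-data analysis is useful if it brings in information that the first did not have, or makes a different assumption. As worded, this one does neither for the primary outcome. A patient with no 24-month scan has no follow-up cartilage volume, so both the primary model and the imputation fall back on baseline variables under missing at random. If dropout depends on how the knee was doing after baseline, both are biased in the same direction, and their agreement could be read as reassurance.

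The sample-size section makes the choice harder to understand. It builds the whole expected effect on BML change driving cartilage loss. By that reasoning the 6-month BML size is a leading predictor of a missing 24-month volume, and it is already collected. Pain at months 3 to 18, knee surgery, joint injections and the withdrawal scan are also collected, and none is named for imputation.

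At the planned dropout, 0.20 × 264 = 52.8, so about 53 patients would lack the primary outcome.

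**Working it through.** **1. Reproduce the plan's own figure (Sample size calculations).**

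- Difference: 928.3 − 824.0 = 104.3 mm³.
- Pooled SD: √[(273.0² + 272.3²)/2] = 272.65 mm³.
- Per arm: 2 × [272.65 × (1.960 + 0.842)/104.3]² = 107.3, so 108.
- With 20% dropout: 108/0.8 = 135, against 132 stated (within 3%).
- Power with 132 × 0.8 = 105.6 completers per arm: 79.4%, against 80% stated.

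The stated size is reproduced and this point does not change it. It does show that the design has no spare power to absorb bias.

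**2. Compare the two analyses for the primary outcome.**

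| | Primary mixed model | Stated imputation |
|---|---|---|
| Information named for missing data | complete baseline variables | complete baseline variables |
| Assumption | missing at random (likelihood-based model) | missing at random |
| Scheduled follow-up cartilage values if the 24-month scan is missing | none | none |

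**3. Check how closely they agree.** Each scenario simulated 1,000,000 patients allocated 1:1.

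- From the plan: true difference 104.3 mm³, SD 272.65, overall dropout 20%, and a treatment shift in the 6-month measure of (198.6 − 22.8)/261.5 = 0.67 SD.
- Assumed, not in the documents: correlation ρ of 0.1, 0.3 or 0.5 between the 6-month measure and 24-month cartilage loss; baseline coefficients of 0.3 (6-month measure) and 0.2 (cartilage change); dropout log-odds slope of 1 per SD; a 6-month value for every patient.
- Method: the primary analysis is represented by a baseline-adjusted regression on completers. Imputation is by arm-specific regression prediction, the large-sample equivalent of multiple imputation with arm included.

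Estimated difference in mm³ for ρ = 0.1 / 0.3 / 0.5 (truth 104.3):

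| Dropout depends on | Baseline-adjusted | Imputation, baseline only | Imputation, baseline + 6-month |
|---|---|---|---|
| baseline | 104.3 / 103.3 / 104.4 | 104.3 / 103.2 / 104.6 | 104.3 / 103.1 / 104.7 |
| 6-month measure, both arms | 101.8 / 99.3 / 94.9 | 101.8 / 99.2 / 94.8 | 104.0 / 105.2 / 104.6 |
| 6-month measure, placebo only | 99.0 / 89.4 / 78.1 | 99.0 / 89.4 / 78.1 | 104.0 / 104.8 / 104.1 |
| 6-month measure, treatment only | 109.2 / 119.0 / 130.1 | 109.2 / 119.0 / 130.1 | 104.0 / 103.8 / 104.3 |
| unobserved 24-month outcome, placebo only | 54.9 / 54.8 / 55.3 | 54.8 / 54.7 / 55.1 | 55.3 / 58.8 / 67.3 |

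Simulation error in each estimate is about 272.65 × √(4/800,000) = 0.6 mm³. The first two columns come from the same simulated patients and never differ by more than about 0.2 mm³. At ρ = 0.3 the one-arm scenarios put both off by about 14%: (104.3 − 89.4)/104.3 downward and (119.0 − 104.3)/104.3 upward. Adding the 6-month measure removes that bias. It does not remove bias that comes from the unobserved outcome itself.

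**4. Pain and BML size.** Pain is scheduled at months 3, 6, 12, 18 and 24, and BML size at 6 and 24. The mixed model uses every observed visit, so someone who leaves after month 12 still contributes pain at months 3, 6 and 12. Imputation from baseline alone would ignore those values and would need missing at random to hold given baseline only, which is the stronger assumption.

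**The case against.** The best counter-argument is that the sentence does not limit imputation to baseline variables. Chained equations impute several incomplete variables in turn and ordinarily condition each on the others. Complete baseline variables could be the fixed predictors, with partly observed pain and BML values entering through the chain. This stands as far as it goes: a reader might infer that post-baseline data are excluded, but the text does not say so. What remains is that the article chose to name the predictors and named only baseline ones.

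A reader might also infer that imputed values will be pulled towards no effect because treatment arm is left out. The documents do not support that. Arm is known for every randomised patient from month 0, so it fits the description of a complete baseline variable, and nothing says that it is omitted.

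A third inference is that the plan has no analysis departing from missing at random. The article condenses a fuller plan, and such an analysis may be in a statistical analysis plan that is not shown. Its absence here carries no weight.

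Finally, the plan calls this a secondary analysis and states its assumption openly. It promises no test of that assumption, and it gives no data on what predicts dropout. Both are fair. They limit the point to how little the stated imputation would add, and do not show that the trial's result will be biased.

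**Conclusion.** The point holds as a criticism of the stated method. For 24-month cartilage volume, imputation from complete baseline variables under missing at random would nearly duplicate the primary analysis (within about 0.2 mm³ in the check), so agreement would say little about bias from 20% dropout. For pain and BML size, imputation from baseline alone would use less information than the mixed model.

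The size of any bias is not known. The range of 78.1 to 130.1 mm³ around 104.3, where dropout follows the 6-month measure, rests on the assumed correlations and dropout slope. Its extremes also need dropout to depend on that measure in one arm only. The near-equality of the two analyses does not rest on the chosen correlation: it appeared at every value and under every dropout mechanism tried. The gain from 6-month data applies only to patients who stay until month 6. If the full imputation model already includes post-baseline data, one clarifying sentence settles the point.

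**What to change.** Replace the sentence on imputation predictors with one to this effect:

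> Multiple imputation by chained equations will include treatment arm (or be run separately by arm), site/scanner, baseline values, and observed post-baseline data: 6-month BML size, pain at months 3 to 18, knee surgery and joint injections, and cartilage volume from any early-withdrawal MRI together with its scan time.

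Keep missing at random as the stated assumption; it is more plausible once these variables are included. As an optional addition, a delta-adjusted analysis of 24-month cartilage volume would address dropout that depends on the unobserved outcome, which no choice of predictors can fully repair.

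The cost is a little more programming and a larger imputation model, which needs care with about 53 missing primary outcomes. No new data are needed, and the sample size and primary analysis do not change.

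### Stratified analyses are meant to show which subgroups respond better, but no treatment × subgroup interaction test is stated

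*Protocol article*

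**What the plan says.** The protocol article deals with subgroups in two sentences of the Statistical analysis section. The first gives both the aim and the method: "Pre-specified stratified analyses will be performed to examine which subgroups may respond better to treatment". The second gives the variables: "Potential stratification variables include radiographic knee OA and co-pathology present on MRI". The sentence after these closes the section with one threshold for everything: "Statistical significance will be set as a two-sided *P* value < 0.05".

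The main model, earlier in the same section, is a "linear mixed model with treatment, month and their interaction (treatment × month) as covariates". Treatment × month carries the longitudinal treatment effect. It does not say whether that effect differs between kinds of patient. The article names no treatment × subgroup term or between-subgroup contrast, and gives no stratum sizes or cut-points.

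**The concern.** The stated method does not answer the stated question. To ask who responds better is to ask whether the treatment effect in one subgroup differs from that in another. A stratified analysis asks, for each subgroup alone, whether the effect differs from zero. Splitting the sample lowers the power in each part, so one stratum can easily be significant and another not when the true effect is the same in both.

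The choice of variables adds to this. They are described as potential, and co-pathology is broad. Under Co-pathology present on MRI it covers cartilage defects graded 0 to 4 at five sites, and meniscal extrusion at three horns on each side. Each further variable or cut-point is another chance of an apparent responder group.

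The Background argues for choosing patients by features that predict response, so a spurious responder subgroup could be carried into later work.

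**Working it through.** **Inputs** (Sample size calculations)
- Expected 24-month cartilage change, each a loss: "824.0 mm^3^ (SD 273.0) in the treatment group" and "928.3 mm^3^ (SD 272.3) in the placebo group".
- Size: "132 patients (allowing for 20% drop out over 24 months) recruited to each arm of the trial".
- Two-sided alpha 0.05, planned power 80%, allocation 1:1.

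**Planning effect**
- Difference: 928.3 − 824.0 = 104.3 mm³.
- Pooled SD: √[(273.0² + 272.3²)/2] = 272.65 mm³.
- Standardised effect: d = 104.3/272.65 = 0.3825.

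**The article's own figure first.** Normal approximation: n per arm = 2(1.960 + 0.842)²/0.3825² ≈ 107.3, so 108 evaluable. Allowing for 20% dropout gives 108/0.8 = 135, or 108 × 1.2 ≈ 130. The stated 132 lies between these. With 132 × 0.8 = 105.6 evaluable per arm, power is Φ(0.3825·√52.8 − 1.96) = 79.4%. The sample size reproduces and is not in question.

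**Two strata with the same true effect.** For n per arm in a stratum, power ≈ Φ(d·√(n/2) − 1.96). With independent strata of power p₁ and p₂, P(exactly one significant) = p₁(1 − p₂) + p₂(1 − p₁).

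Equal split: n = 52.8 and 0.3825·√26.4 = 1.965, so power is 50.2% in each. Then 2 × 0.502 × 0.498 = 0.50.

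The article gives no stratum sizes, so the split is an assumption. The range is:

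| Split | Power, larger | Power, smaller | Exactly one significant |
|---|---|---|---|
| 50:50 | 50.2% | 50.2% | 50.0% |
| 60:40 | 57.7% | 42.0% | 51.2% |
| 70:30 | 64.3% | 33.1% | 54.8% |
| 80:20 | 70.1% | 23.7% | 60.5% |
| 90:10 | 75.1% | 14.2% | 68.0% |

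With three equal strata, power is 36.1% in each. The chance that some but not all are significant is 1 − 0.361³ − 0.639³ = 69%.

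**Smaller true effects on cartilage volume**
- Half the planned effect: power is 16.6% in each of two equal strata, so 2 × 0.166 × 0.834 = 27.7%. Across the splits above the range is 28-30%.
- No effect: 2 × 0.05 × 0.95 = 9.5%. For benefit in one stratum only it is 2 × 0.025 × 0.975 = 4.9%.

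**Pain and BML size.** The Secondary outcome paragraph gives powers of 98.9% and 99.6%.
- Pain: noncentrality 2.29 + 1.96 = 4.25. Halving the sample divides it by √2, giving 3.01 and power of about 85%. Exactly one of two: 2 × 0.85 × 0.15 ≈ 25%.
- BML size: 2.65 + 1.96 = 4.61, divided by √2 is 3.26, with power of about 90%. Exactly one of two: about 17%.

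**Interaction test for comparison.** The test divides the difference between the two stratum effects by its standard error, 272.65·√(4/52.8) = 75.0 mm³. In a simulation of 40,000 trials with 53 per arm per stratum and equal effects, it was significant in 5.0% under the planned effect and 5.2% under no effect. At the planned effect, only about 10% of trials with exactly one significant stratum also had a significant interaction.

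Its power for a true between-subgroup difference of 104.3 mm³ at 50:50 is Φ(104.3/75.0 − 1.96) = 28%.

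**The case against.** The strongest reply is that this treats silence as a decision. The article condenses a fuller plan. It says neither that strata will be compared by their P values nor that no interaction test will be run, and the final variables, cut-points and contrasts are often left to the SAP. The 0.05 threshold closes the whole section and is not tied to within-stratum tests. A reader might infer that interaction testing has been ruled out, or that a subgroup will be declared a responder because it alone is significant. The text supports neither. Nor do pre-specified and potential contradict each other if the list is closed in a document not shown.

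A reader might also take 50% as the general error rate. It belongs to cartilage volume, at the full planned effect, with two equal strata. With little or no true effect it is much lower, and at the stated powers it is lower for pain and BML size.

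Finally, the phenotype behind the trial is the bone-specific one. It is applied at enrolment, since a BML on MRI is an inclusion criterion. Radiographic OA and co-pathology are further exploration, and no confirmatory subgroup claim is announced.

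These replies limit the size and wording of the point. They do not remove it. The article does state an aim and a method, the method does not serve the aim, and the one interaction it names addresses something else.

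**Conclusion.** The point holds in a conditional form. The article plans stratified analyses for a question about differences between subgroups and states no test of such differences. If strata are compared by which one reaches P < 0.05, a uniform effect on cartilage volume at the planned size will look like a subgroup difference in about half of trials for each two-level variable. That is ten times the rate of an interaction test. Unequal strata raise the figure. A smaller true effect lowers it, to about 10% at no effect.

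The figures rest on four assumptions:
- the comparison-by-significance rule, which is an inference;
- the assumed stratum sizes;
- a two-sample comparison of 24-month change standing in for the mixed model, which is reasonable for cartilage volume because it is calculated only at screening and 24 months;
- for pain and BML size, the stated powers taken as they are. The article does not say whether these allow for dropout. If they do not, power per stratum would be lower and the rates higher.

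**What to change.** Keep the planned linear mixed model. For each subgroup variable, add treatment × month × subgroup with its lower-order terms. Then:
- base any statement that a subgroup responds better on the between-subgroup difference in the 24-month treatment effect, with its 95% CI;
- show stratum estimates with intervals for description only;
- close the list of baseline variables and their cut-points before unblinding (which variables to choose is for the investigators);
- label all subgroup results exploratory.

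If the SAP already contains this, one sentence pointing to it is enough.

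The change needs no new data or visits, only analysis wording. Its real cost is low power: about 28% for a between-subgroup difference of 104.3 mm³ at 50:50, a difference as large as the whole planned treatment effect. Fewer subgroup claims will be possible, and a non-significant interaction must not be read as evidence that the effect is the same in all patients.
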